## Abstract

Obesity and depression are highly prevalent diseases that are strongly correlated. At the same time, there is a growing gap in care, and treatment options should be improved and extended. Positive effects of a Mediterranean diet on mental health have already been shown in various studies. In addition to the physiological effects of nutrients, the way food is eaten, such as mindful eating, seems to play a role. The present study investigates the effect of a Mediterranean diet and mindful eating on depression severity in people with clinically diagnosed major depressive disorder and obesity. Participants will be randomised to one of the four intervention groups (Mediterranean diet, mindful eating, their combination and a befriending control group). The factorial design allows investigating individual effects as well as potential synergistic effects of the interventions. The study consists of a 12-week intervention period, where five individual appointments will take place, followed by a 12-week follow-up. The primary outcome is depression severity. Secondary outcomes are remission of depression, assessor-rated depression severity, quality of life, self-efficacy, BMI, waist:hip ratio and body composition; adherence to the Mediterranean diet and mindful eating will also be assessed. Alongside mediator and moderator analysis, a microbiome analysis, a qualitative evaluation and an economic analysis will be conducted. The study investigates an important health issue in a vulnerable target group. It allows to draw valuable conclusions regarding the effectiveness of different interventions and therefore contributes to improving available care options for people suffering from depression and obesity.

Mental health and dealing with mental illness are becoming increasingly important. The point prevalence of mental disorders increased by 48·1 % between 1990 and 2019 and has reached 12·3 % worldwide^(1)^. In Germany, the lifetime prevalence of depression is 11·6 %^(2)^, with major depression as one of the most common forms. Another present emerging burden of health is obesity. Since 1990, the prevalence in Germany has more than doubled; in 2019, 19·0 % of the German population suffered from obesity^(3)^. The COVID-19 pandemic had a major negative impact on both diseases. Calculations result in 53·2 million additional cases of major depression worldwide^(4)^ and a 3 % increase in the prevalence of obesity^(5)^.

Obesity and depression are significantly correlated with each other^(6)^. Both diseases are predictors of the development of the other. The correlation is stronger with higher grades of BMI and higher severity of depressive symptoms^(7,8)^, indicating a dose–response relationship. Besides social factors^(9)^, shared biological mechanisms including genetic, endocrinology and immunological-inflammatory factors and the microbiome can explain the co-occurrence^(10,11)^.

The availability of treatment options for both diseases is inadequate. To receive adequate therapy, personal and financial efforts and long waiting times are often required^(12,13)^. Additionally, 20–40 % of depression patients are considered non-responders for standard treatment^(14)^. Weight reduction programmes often fail to reach clinical relevance, especially in the long term^(15)^. Prevalence increases with decreasing income and education status^(2,3,9)^, and motivation problems and exhaustion, which often go hand in hand with depression^(16)^, further exacerbate the vicious circle. The urge for low-threshold, easily accessible therapy approaches becomes clear.

An uprising field of research is the influence of diet on mental health. The most popular dietary pattern in this context is the Mediterranean diet. Its effect on depression has already been investigated in a number of randomised controlled trials. A significant improvement in depressive symptoms through Mediterranean diet interventions was shown in the SMILES (Supporting the Modification of lifestyle in Lowered Emotional States), HELFIMED (Healthy Eating for Life with a Mediterranean-style diet) and AMMEND (A Mediterranean Diet in MEN with Depression) trials^(17–19)^. A recent meta-analysis shows a moderate, significant effect in the reduction of depression severity^(20)^. Two further meta-analyses show an inverse relationship between adherence to the Mediterranean diet or a healthy dietary pattern and the onset of depression^(21,22)^.

Regarding obesity, many health benefits of the Mediterranean diet have been described, including weight loss, the reduction of visceral adipose tissue, oxidative stress and inflammation and modulation of the gut microbiome^(23)^. These pathophysiological processes have also been named in the context of depression and obesity^(10,11)^. Also, a positive influence of weight loss programmes on depressive symptoms and mental health in people with overweight and obesity is described^(24,25)^.

The concept that it is not only *what* is eaten that counts but also *how* it is eaten is embodied as mindful eating. Mindful eating is defined as persistent attention to sensory elements of eating, a non-judgemental awareness of thoughts and feelings while eating, awareness of hunger and satiety, finding a quiet place and avoiding distractions^(26,27)^.

A mediator analysis shows a direct effect of mindful eating on depression severity. The effect of three of four mindful eating domains (focused eating, eating with awareness, eating without distraction) on depression severity is mediated neither by adherence to the Mediterranean diet nor by energy intake independent of BMI^(28)^. In a systematic review, positive effects on binge eating, emotional eating and eating in response to external stimuli through increased mindfulness are described^(29)^. A meta-analysis shows that mindfulness interventions have a positive effect on eating behaviour, depression and weight loss in people with overweight and obesity^(30)^.

In summary, it can be said that depression and obesity are highly prevalent diseases that negatively impact each other and are correlated in various social and pathophysiological ways. People affected are in need of long-term, effective treatment, but therapy options are scarce and sometimes hardly accessible. A positive effect of the Mediterranean diet, as well as mindful eating, on both conditions has already been shown. However, their synergetic effects remain unclear. The planned study now investigates their separate and combined effect in the target group of people with co-morbid depression and obesity. It provides important insights not only on the effectiveness of the different interventions but also into potential synergetic effects and therefore contributes to improving available therapy options for people suffering from depression and obesity.

## Objective

The primary aim of this study is to investigate the efficacy of the Mediterranean diet and/or mindful eating on depression severity in people with clinically diagnosed major depressive disorder and obesity. The study design allows separate and combined investigation of physiological and psychological aspects of a nutritional intervention in order to identify possible synergistic effects. In secondary analyses, moderator and mediator analysis, microbiome analysis and economic evaluation of the intervention will be conducted. The feasibility of the intervention, as well as the requirements and needs of the target group in relation to the interventions, will be examined in a qualitative approach.

## Methods

### Study design

The study is designed as a 2 × 2 factorial randomised controlled intervention trial. The four intervention groups consist of Mediterranean diet (yes/no) and mindful eating (yes/no). The intervention lasts 12 weeks, followed by a 12-week follow-up. Outcome assessment and data analysis are conducted by blinded study personnel.

### Ethical approval, trial registration and trial status

The study follows Good Clinical Practice principles in line with the Declaration of Helsinki^(31)^. Ethical approval was obtained by the ethics committee of the University of Tübingen (331/2024BO1). The trial was prospectively registered on Clinical Trials (registration number NCT06621394). Registration follows the suggestions of the WHO Trial Registration Data Set. The study is starting recruitment in October 2024 (first patient in) and is expected to end in December 2026 (last patient out).

### Study setting

The study will take place at the Bosch Health Campus in Stuttgart, Germany. The interventions will be conducted in five personal one-on-one appointments.

## Recruitment and study enrolment

Participants will be recruited in the Department of Psychosomatic Medicine of the Robert Bosch Hospital, Stuttgart, and via social media. Information about the study can be obtained from a website. People interested in participation can contact the study centre. After checking for the main inclusion criteria by phone or digitally (pre-screening), they will be invited for the inclusion examination and will provide written informed consent. In case of inclusion, an appointment for baseline measurement and the first intervention appointment will be made. An overview of enrolment, intervention and assessment is given in Fig. 1.

**Fig. 1. f1:**
[figure not shown]
Overview of enrolment, interventions and assessments. EQ-5D-5L, European Quality of Life 5 Dimensions 5 Level.

For microbiome analysis, additional samples of healthy controls (i.e. free of depression and obesity) will be collected. Inclusion of participants without depression and obesity allows better interpretation of the results from microbiome analysis and its potential changes over the intervention. They will be recruited from employees of the Robert Bosch Hospital via email. Healthy controls will come to the study centre to obtain written informed consent and fill in questionnaires. In case of inclusion, they will be handed the necessary materials for collecting the stool sample. When the sample is handed back in, participants will be reimbursed with a 20€ voucher. They will not receive any intervention.

## Study population

Study participants are adults with major depressive disorder and obesity.

### Inclusion criteria

Age ≥ 18 yearsDiagnosis of major depressionAt least moderate depression severity: Beck Depression Inventory – II (BDI-II) ≥ 20Obesity: BMI ≥ 30 kg/m^2^
Stable co-intervention: no change in the type, dosage or frequency of antidepressant medication and/or psychotherapy 4 weeks before the study and no plans to change in the next 12 weeksMedium to low adherence to the Mediterranean diet: Mediterranean Diet Adherence Score < 10Medium to low adherence to mindful eating: Mindfulness Eating Inventory < 5·13

*Given no previous cut-off scores, for the purpose of this study, we have defined the cut-off value of < 5·13 as the inclusion criterion corresponding to the mean value of the norm population plus 2 sd
*
^(27)^.

### Exclusion criteria

Diseases of the gastrointestinal tract that do not allow adequate implementation of the intervention (e.g. irritable bowel syndrome, colorectal carcinoma)Metabolic diseases with a strong impact on intervention (e.g. type 1 diabetes mellitus, chronic kidney disease)Severe food allergies and intolerances that do not allow adequate implementation of the interventionDiagnosed, current psychological co-morbidities (bipolar disorder, eating disorder, personality disorder, psychosis)Intake of antibiotics during the last 3 monthsDiagnosed, current substance abusePregnancy or breastfeedingAcute suicidal ideationUnable to participate or to complete questionnaires

### Healthy controls for microbiome analysis

For healthy controls, the following inclusion and exclusion criteria are defined:

#### Inclusion criteria

Age ≥ 18BMI 20–30 kg/m^2^

#### Exclusion criteria

Depression (BDI-II ≥ 20) or other psychological co-morbidities (bipolar disorder, eating disorder, personality disorder, psychosis)High adherence to Mediterranean diet (Mediterranean Diet Adherence Score ≥ 10)High adherence to mindful eating (Mindfulness Eating Inventory ≥ 5·13)Severe chronic metabolic disease or disease of the gastrointestinal tract (e.g. irritable bowel syndrome, diabetes mellitus type 1)Intake of antibiotics during the last three monthsSubstance abusePregnancy or breastfeeding

## Randomisation

After inclusion, participants are randomised to one of the four intervention groups. Randomisation is performed using a randomisation list with varying block lengths (4, 8, 12) created by the programme R. Group allocation is carried out by members of the research staff via RedCap. Therefore, allocation concealment is given. Severity of obesity (obesity grade 1: BMI 30–35 kg/m^2^; obesity grade 2–4: BMI ≥ 35 kg/m^2^) and severity of depression (moderate depression: BDI-II 20–28; severe depression: BDI-II ≥ 29) are defined as strata. Participants are assigned to one of the four intervention groups in a 1:1:1:1 ratio. Participants will be informed about the group assignment at their first intervention appointment.

## Sample size calculation

Sample size calculation was carried out with the programme R Version 4.4.0, package ‘pwrss’ version 0.3.1. It is based on effect sizes of comparable interventions of the Mediterranean diet^(32)^ and mindful eating^(33)^ on the primary outcome of the study (BDI-II score). Using a conservative approach, we have used the lower effect size of d = 0·86 of the mindfulness intervention (Mediterranean diet: d = 1·7) to compute the required sample size. Considering a statistical power of *β* = 0·8 and *α* = 0·05, as well as a 20 % dropout rate for ANCOVA with main and interaction effects and baseline scores as covariate, *n* 64 subjects need to be recruited, that is, sixteen participants in each group.

For microbiome analysis, samples of *n* 32 healthy controls will additionally be analysed, representing the same number of participants receiving each intervention.

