## Statistical analysis

The statistical analysis will be carried out using the programme R version 4.4.0. As a significance level, p ≤ 0·05 is defined. Data will be analysed as an intention-to-treat analysis. To handle missing data, the ‘missForest’ package in R will be used. This package implements a non-parametric imputation method based on random forests. This approach iteratively imputes missing values using a predictive model that leverages relationships among observed data while accounting for both continuous and categorical variables. Default settings for the algorithm will be used, which automatically selects the optimal number of trees and variables per split to maximise imputation accuracy. The primary outcome parameter is analysed confirmatory using a two-factorial ANCOVA, in which the main outcome parameter is modelled as a function of the two factors – mindful eating (yes/no) and Mediterranean diet (yes/no) – and the respective baseline values (linear covariates). Both main effects of the interventions and interactions are considered. Secondary outcomes will be exploratory (without correction for multiple testing) and analysed using the same models as the primary outcome. To estimate the clinical significance of the results, change scores and effect sizes (Hedges’ g) are calculated for between-group comparisons. The clinical relevance of the results is examined by comparing the number of participants who achieve a clinically relevant improvement of at least 5 points^(51)^ on the BDI-II between the groups at week 12 and week 24 using a logistic regression adjusted for the BDI-II baseline value (random effect). The same model is used to compare the number of patients between the groups who reach remission of depression at week 12 and week 24 (BDI-II < 9).

Mediator and moderator analyses are conducted with the PROCESS Package^(52)^. For the mediator analysis, the indirect effect of an independent variable on a dependent variable via a mediator and its significance are tested using the bootstrap method. Mediation paths can be identified and quantified with consideration of control variables. Concerning moderator analysis, the relationship between the moderator and the independent variable is analysed using product terms in the regression model. Strength and direction are determined using coefficients and statistical significance using the bootstrap method.

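### The stated 80 % power is attached to main and interaction effects alike, but at d = 0.86 it holds for the two main effects and not for an interaction of that size

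*Protocol article*

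**What the plan says.** The Sample size calculation section of the protocol article takes published effects of single interventions on the BDI-II: "It is based on effect sizes of comparable interventions of the Mediterranean diet", and likewise of mindful eating. Of the two, "we have used the lower effect size of d = 0·86 of the mindfulness intervention", the Mediterranean diet value being 1.7. The target is set as "Considering a statistical power of *β* = 0·8 and *α* = 0·05". The same sentence then allows for a loss of 20 % and names the analysis that the calculation serves: "dropout rate for ANCOVA with main and interaction effects and baseline scores as covariate". The result is 64 recruited, 16 per group. No effect size for the interaction and no correlation between baseline and follow-up BDI-II is given.

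The interaction matters to the trial. The Abstract says: "The factorial design allows investigating individual effects as well as potential synergistic effects of the interventions". The Objective section describes separate and combined investigation "in order to identify possible synergistic effects". The introduction presents the joint effect of the two interventions as the open question. The Statistical analysis section puts both main effects and the interaction into the confirmatory two-factor ANCOVA of the BDI-II, with the rule "As a significance level, p ≤ 0·05 is defined".

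**The concern.** As printed, the sentence lets a reader take 80 % power at d = 0.86 for every term it names, the interaction included. In a balanced 2 × 2 design that cannot be so for an interaction of the planning size. The interaction contrast has twice the standard error of a main effect, so the same number of SDs is much harder to detect.

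At stake is how the synergy result can be read. A non-significant interaction from a trial that appears to have 80 % power for it looks informative. With the power actually available at 0.86 SD, it would say little. The power statement should not invite that reading.

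**Working it through.** **Inputs.** From the Sample size calculation section: d = 0.86, α = 0.05, power 0.80, dropout 20 %, 64 recruited, one baseline covariate. From Randomisation: 1:1:1:1. Analysed after dropout: 64 × 0.8 = 51.2, taken as 51. Assumed, because the article does not give it: either d is already on the residual SD scale (no further gain from the covariate), or d is in raw SD and baseline correlates ρ = 0.3, 0.5 or 0.7 with the outcome.

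**Method.** Non-central F with 1 and N − 5 degrees of freedom (four cells, one covariate), non-centrality λ = N·f².

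**Step 1: the plan's own figure.** A main effect compares two halves of the sample, so f = d/2 = 0.43.
- N = 44 gives 79.4 % and N = 45 gives 80.4 % (λ = 45 × 0.1849 = 8.32), so 45 must be analysed.
- Recruited: 45/0.8 = 56.25, so 57. With equal groups, 48/0.8 = 60.
- The stated 64 is not reproduced, but it lies above both figures. A 3-df test of all four groups at f = 0.43 does give 64, but as the number analysed, before any dropout (64/0.8 = 80 recruited).

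**Step 2: main-effect power with 64 recruited.**
- 51 analysed: λ = 51 × 0.1849 = 9.43, power 85.2 %.
- 64 analysed: λ = 11.83, power 92.3 %.

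The 80 % target is met.

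**Step 3: the interaction.** Define it as the effect of one intervention when the other is given, minus its effect when the other is not given.
- Each cell mean has variance σ²/(N/4). Four of them give 16σ²/N, so SE = 4σ/√N.
- A main effect has SE = 2σ/√N, half as large.
- Hence f = δ/4 for an interaction δ in SD units. For δ = 0.86, f = 0.215.
- 51 analysed: λ = 51 × 0.0462 = 2.36, power 32.4 %. A simulated ANCOVA (4,000 runs) gave 31.9 %.
- 64 analysed: λ = 2.96, power 39 %.
- 80 % power would need 172 analysed, or 172/0.8 = 215 recruited.

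**Step 4: gain from the baseline covariate.** If 0.86 is in raw SD, f becomes 0.215/√(1 − ρ²).

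| Analysed | no gain | ρ = 0.3 | ρ = 0.5 | ρ = 0.7 |
|---|---|---|---|---|
| 51 | 32 % | 35 % | 41 % | 56 % |
| 64 | 39 % | 43 % | 50 % | 66 % |

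Reaching 80 % would take ρ of about 0.84 (51 analysed) or 0.80 (64 analysed).

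**Step 5: what is detectable.** On the residual scale, 80 % power needs f = 0.4008 at N = 51, that is 4 × 0.4008 = 1.60 SD. At N = 64 it needs f = 0.3561, that is 1.42 SD.

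**The case against.** The strongest reply is that naming main and interaction effects only lists the model terms, matching the Statistical analysis section, and makes no power claim for the interaction. That reading is possible. But then a stated aim has no power figure, and the sentence still attaches 80 % to a model without saying for which term.

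A second reply is that a power routine returns the same N for any 1-df term if f = 0.43 is entered. That is true, and a reader might infer that this was done. The article does not say so. If it was, the arithmetic is right for that f, but for the interaction f = 0.43 means 4 × 0.43 = 1.72 SD, twice the planned effect of a whole intervention, and nothing in the section supports that size.

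Third, the 0.86 SD for the interaction is this review's benchmark, and 32 % is the low end of a range that depends on an unstated correlation. This stands, so the range should be quoted and not 32 % alone.

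Some stronger readings are tempting but unsupported:
- That synergy is the trial's declared novelty. The Discussion names the co-morbid population and the separate evaluation of what is eaten and how, which is the main-effects question.
- That the investigators will conclude there is no synergy from a non-significant interaction. No section plans this, and the Abstract and Objective speak only of potential or possible synergy.
- That 64 is too few for what it was computed for. For main effects at d = 0.86 it is more than the inputs require.

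**Conclusion.** The point holds as a defect in the power statement, not in the main-effect sample size. With 64 recruited, the 80 % is met for each main effect at 0.86 SD (about 85 % with 51 analysed). It does not extend to an interaction of 0.86 SD, where power is 32 % to 56 % with 51 analysed and 39 % to 66 % with all 64. Every case examined is below 80 %.

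This rests on the interaction being a difference of differences on the same SD scale as d, on equal cells, and on ρ between 0.3 and 0.7 where a covariate gain is allowed. The main-effect figure assumes 0.86 SD averaged over the levels of the other factor; if the combination is less than additive, the main effect shrinks as well. The 64-analysed figures are an upper bound under 20 % dropout, because imputing missing outcomes adds no information from those who left.

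This should be fixed. It is not critical, since the remedy changes neither the sample nor the primary model. The derivation of 64 is a side point: it does not follow from the stated inputs, but it errs on the safe side for the main effects.

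**What to change.** Keep 64 and make these changes in the text:
1. Limit the 80 % statement to the two main effects at d = 0.86.
2. State the interaction detectable with 80 % power (about 1.6 SD with 51 analysed, 1.4 SD with 64, residual scale). Give the power range at 0.86 SD, and say which SD scale and which baseline correlation are assumed.
3. State that the interaction will be reported as an estimate with a 95 % CI, and that a non-significant result will not be taken as evidence of no synergy.
4. Show how 64 was obtained, since the stated inputs give 57, or 60 in equal groups.

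The cost is wording only: no extra participants and no change to the primary model. The stated power for the synergy question becomes less favourable.
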